### ***Quality of Life***

The 12-item Short Form Health Survey (SF-12) was administered in this study. The SF-12 consists of 12 items and includes eight dimensions of general health (GH), physical functioning (PF), vitality status (VT), mental health (MH), somatic pain (BP), somatic role restriction (RP), emotional role restriction (RE), and social functioning (SF). The PF, RP, BP, and VT dimensions compose the physical component summary (PCS), and the GH, SF, RE, and MH dimensions compose the mental component summary (MCS). The scores of each dimension and the total PCS and MCS scores were calculated sequentially, with a total possible score of 100; higher scores indicate better self-perceived quality of life for patients.

### **Blood lipid indices**

The following measurements were taken at hospital admission and during follow-up visits: body weight and height, which were used to calculate lipid values (total cholesterol (TC), high-density lipoprotein cholesterol (HDL-C), low-density lipoprotein cholesterol (LDL-C), and triglyceride (TG) level).

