159 research team will ensure that patients have signed the informed consent form before  
160 entering the study and will provide ongoing support and guidance throughout the  
161 study.

162 After the recruitment and pre-screening processes, patients were divided into two  
163 groups based on their admission dates: the control group (April to May 2022) and the  
164 intervention group (May to June 2022). In addition to receiving standardized  
165 treatment, the intervention group also received a multidimensional digital cardiac  
166 rehabilitation intervention, which encompassed seven dimensions: exercise training,  
167 medication management, nutritional guidance, psychological support, sleep  
168 management, health education, and smoking cessation support. It is important to note  
169 that, in addition to the intervention for patients themselves, the digital cardiac  
170 rehabilitation intervention particularly emphasized the involvement of the patients'  
171 family members. During the hospitalization period, family members were invited to  
172 participate in the rehabilitation training program, ensuring that they could provide

necessary support for the patients and promote health education within the home environment. The control group, on the other hand, received only standardized treatment and standard nursing care.

After the PCI procedure, both groups of patients underwent a three-month follow-up period. The follow-up included individualized educational sessions conducted monthly via the WeChat platform, in addition to outpatient visits at one and three months post-surgery. During the follow-up, patients were required to report their health status to the multidisciplinary intervention team, including blood pressure, physical activity, dietary habits, sleep patterns, psychological state, and progress in smoking cessation.

Only patients who completed all data collection requirements were included in the final analysis. The final dataset was subjected to propensity score matching to balance the baseline characteristics between the two groups, ensuring comparability.

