### ***1.2. Medication Management***

Effective medication management is essential for improving outcomes following PCI, and in the intervention group, nurses provided comprehensive medication education to ensure that patients understood the importance of their prescribed treatments. This education covered the correct timing, dosage, and potential side effects of medications, along with guidance on how to manage and adjust medications based on specific health indicators such as blood pressure and blood glucose levels. Nurses held one-on-one sessions twice a week to reinforce medication adherence, clarify any misconceptions, and ensure patients fully understood their treatment regimens.

In addition to medication education, patients were informed about behaviors that could help maintain their health and support recovery. Videos featuring healthcare practitioners were used to explain the role of medications like statins, aspirin, and Tegretol in stabilizing coronary arteries, alongside information about other common medications such as angiotensin-converting enzyme inhibitors and receptor blockers. Educational content also included guidance on adopting a healthy lifestyle, including the importance of diet, exercise, smoking cessation, and returning to normal activities and work. This information was provided through an interactive mind map accessible via QR codes, aimed at helping patients navigate their recovery process and alleviate anxiety related to their condition.

The comprehensive approach to medication management was part of a broader

strategy to empower patients with the knowledge and tools necessary to take control of their health. By combining education on medication with lifestyle advice, this intervention aimed to improve both adherence to prescribed treatments and overall well-being during recovery.

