### **Randomization**

Owing to the nature of the intervention, the participants were not randomly assigned. To minimize potential confounding factors, the multidimensional digital cardiac rehabilitation intervention group and the usual care group were matched on the basis of propensity scores calculated using logistic multiple regression analysis. The matching process involved considering covariates such as age, sex, education level, marital status, exercise habits, monthly salary, current address, living arrangement

(solitary or not), history of CHD, history of PCI, length of hospitalization, medical insurance status and polypharmacy data obtained from presurveys. Propensity score analysis was conducted using a 1-to-1 ratio matching approach with the nearest neighbour method to ensure balanced characteristics between the intervention and control groups. A standard calliper width of 0.2 was used for the propensity score. After matching, a total of 136 patients were included, with 68 patients in the multidimensional digital cardiac rehabilitation group and 68 patients in the usual care group.

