### **Study Outcome**

All clinical outcome measurements were obtained at the three-month follow-up. The primary outcomes included differences in the 6MWT, the SF-12 scores, and the frailty phenotype scores. Secondary outcomes comprised step speed, 30s-CST, grip strength, WC, BMI and changes in lipid profiles (TC, HDL-C, LDL-C, and TG) at 3 months.

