## Discussion

Findings indicated that a multidimensional digital CR intervention improved functional status (FP, 6MWT, gait speed, and 30-s CST) and metabolic markers (TC, TG, and LDL-C) in patients with UA undergoing PCI within a relatively short period compared to standard management. These results emphasize the program's potential to enhance physical recovery and cardiovascular health. Significant time effects were also observed for grip strength, WC, BMI, and overall quality of life (physical and mental components), reinforcing the efficacy of digital interventions. This novel rehabilitation model provides CVD education, clarifies essential diagnostic procedures, provides exercise rehabilitation guidance, and supports home-based rehabilitation. Promoting physical activity, encouraging lifestyle modifications, and facilitating behavioral changes during recovery contribute to improved quality of life in patients with UA undergoing PCI.

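### The claimed TC, TG and LDL-C benefit is not protected against a difference between the two admission-date cohorts in lipid-lowering therapy at admission

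*Combined protocol and SAP*

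**What the plan says.** All references are to the combined protocol and SAP.

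- **Allocation.** Study Design divides patients into "groups based on their admission dates: the control group (April to May 2022) and the" intervention group (May to June 2022). The Randomization section confirms: "Owing to the nature of the intervention, the participants were not randomly assigned".
- **Confounding control.** The same section describes 1:1 nearest-neighbour matching on a propensity score. The listed covariates end with "history of PCI, length of hospitalization, medical insurance status and polypharmacy data obtained from presurveys". The list names no lipid-lowering drug and no baseline lipid. It is introduced as a set of examples, so it may not be complete.
- **Endpoint.** Study Outcome lists as secondary "changes in lipid profiles (TC, HDL-C, LDL-C, and TG) at 3 months". Blood lipid indices gives admission and the follow-up visits as the measurement times, so the change is from admission.
- **Analysis.** Statistical Method describes t tests or Wilcoxon tests for continuous variables, with significance at P < 0.05. It describes no covariate-adjusted model.
- **Claim.** The Discussion reports that the programme improved "metabolic markers (TC, TG, and LDL-C) in patients with UA undergoing PCI within a relatively short period compared to standard management".
- **Drug content of the programme.** Section 1.2, Medication Management, includes adherence sessions and videos that "explain the role of medications like statins, aspirin" and other drugs.
- **Measurement method.** The only method text for the lipids says that the measurements were "body weight and height, which were used to calculate lipid values (total cholesterol (TC" and the other three lipids.

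**The concern.** A patient who starts lipid-lowering therapy after admission and one who was already treated would be expected to show different lipid changes over three months, whatever rehabilitation they receive. If the May-June cohort held more patients untreated at admission than the April-May cohort, the intervention group would show the larger average fall even if the programme had no effect on lipids. The opposite imbalance would hide a real effect.

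Matching is the only safeguard, and the listed covariates do not address this. A polypharmacy variable does not show whether a lipid-lowering drug is among the medicines. The baseline lipid value would carry some of the same information, but it is not in the list and not in the described analysis. What is at stake is the attribution in the Discussion, which credits the lipid result to the programme without qualification.

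**Working it through.** The documents give no lipid SD, effect size, power statement or numeric lipid result, so there is no design figure to reproduce. The sample counts agree: 89 + 75 = 164 before matching and 68 + 68 = 136 after.

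**Inputs**

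| Input | Value | Source |
|---|---|---|
| Matched patients per group | 68 | Randomization |
| Significance level | 0.05, two-sided | Statistical Method; sidedness assumed |
| SD of LDL-C change | 0.8 to 1.0 mmol/L | assumption |
| Extra fall in new starters | 0.8 to 1.2 mmol/L | assumption |
| Imbalance in new starters | 10 or 20 percentage points | assumption |

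**Step 1. Standard error of the group difference.** SE = SD × √(2/68) = SD × 0.1715. This is 0.137 mmol/L for SD 0.8 and 0.171 mmol/L for SD 1.0.

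**Step 2. Shift from the imbalance.** Shift = imbalance × extra fall.
- 10 points: 0.10 × 0.8 = 0.08 to 0.10 × 1.2 = 0.12 mmol/L.
- 20 points: 0.20 × 0.8 = 0.16 to 0.20 × 1.2 = 0.24 mmol/L.

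**Step 3. False-positive rate with no programme effect and a systematic imbalance of that size.** Rate = P(|Z + shift/SE| > 1.96).

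| Imbalance | Mildest case (SD 1.0, fall 0.8) | Strongest case (SD 0.8, fall 1.2) |
|---|---|---|
| 10 points | shift/SE = 0.466; rate 7.5% | shift/SE = 0.875; rate 14.1% |
| 20 points | shift/SE = 0.933; rate 15.4% | shift/SE = 1.749; rate 41.7% |

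**Step 4. Imbalance that alone gives an expected difference at the significance threshold.** The threshold is 1.96 × SE = 0.269 mmol/L (SD 0.8) or 0.336 mmol/L (SD 1.0). Dividing by the extra fall gives 0.269/1.2 = 22 points at the strongest and 0.336/0.8 = 42 points at the mildest. A moderate imbalance would therefore explain part of a significant difference. Explaining all of it would take a large one.

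**Step 5. Chance imbalance is a different matter.** If new-starter status varies only by chance, it is part of the outcome's own variability and the test already allows for it. Simulating no effect with 68 per group and an assumed 40% new starters gave an overall false-positive rate of about 5% at both extremes of the inputs. The rates in Step 3 apply only if the two cohorts differ systematically.

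**The case against.** The strongest case on the other side is that a large drug difference is unlikely. Both cohorts come from one department in adjacent months. Intervention Strategy provides guideline-based standardized treatment to all patients. Previous PCI is an exclusion criterion in both groups. Polypharmacy is matched, the covariate list may be incomplete, and Results reports no significant baseline differences after matching.

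Much of this stands, and it makes a 20-point gap speculative. It does not close the question. Standardized treatment during the study does not determine who was already treated on arrival, and change from admission depends on that. Nothing shows that lipid-lowering therapy was among the variables matched or compared. Had it been compared, non-significance would be weak reassurance: at an assumed 40% prevalence the SE of the difference is √(2 × 0.4 × 0.6/68) = 0.084, so a gap of about 16 points (1.96 × 0.084 = 0.165) would still pass.

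The Discussion also mentions time effects for other outcomes, so some repeated-measures analysis may have been run. Statistical Method does not describe one, and it would not by itself account for therapy at admission.

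A further objection is that drug use is part of what the programme tries to improve. That is correct for use after the programme starts, which is partly an intended pathway. It does not apply to therapy already in place at admission.

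A reader might infer three stronger points that the documents do not support:
- **That the lipid benefit is a drug artefact.** The documents contain no data on lipid-lowering therapy by group, so they neither show nor exclude this.
- **That chance imbalance alone inflates the error rate.** It does not (Step 5 of the working).
- **That the lipid values are invalid because they were derived from weight and height.** The section is headed as blood indices, and weight and height are the BMI inputs under Physical Fitness. Merged text is the likely explanation, and it has no bearing on confounding.

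**Conclusion.** The concern holds in a limited form. For TC, TG and LDL-C, the described analysis cannot separate a programme effect from a pre-existing difference in lipid-lowering therapy between cohorts formed by date. The size and direction of any such difference are unknown. On the assumed SD and drug-related fall, a systematic 10-point imbalance would move the LDL-C difference by 0.08 to 0.12 mmol/L and raise the false-positive rate from 5% to about 8-14%. The imbalance is itself an assumption, and the figures are for LDL-C only.

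These are secondary endpoints, so the primary outcomes do not depend on this point. It matters because the Discussion draws an effect conclusion from the lipids. The measurement sentence is a separate and smaller defect: as written, it leaves four endpoints without a usable method.

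**What to change.** 1. Compare each of the four lipids with a model adjusted for its baseline value and for lipid-lowering therapy at admission (yes or no). Blood lipid indices says measurements were taken at admission. Therapy at admission would come from the electronic health records that Informed Consent says are accessed. If therapy was in fact one of the matching covariates, state this and show its balance.
2. Do not adjust for drug use after the programme starts. Show use at discharge by group as descriptive data, and at three months if it was recorded. The follow-up self-reports listed in Study Design include no medication item, so the three-month data may not exist.
3. Limit the lipid statement in the Discussion to what remains after adjustment. If the records lack the field, state that a drug difference between the cohorts cannot be excluded.
4. Correct the sentence in Blood lipid indices. The sponsor should confirm how the lipids were measured and add the method.

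The cost is a small record extraction for the matched patients, two covariates in four secondary comparisons, and two text corrections. The downside is that the lipid effect may shrink.

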### **Statistical Method**

Statistical analysis was performed using R (4.2.0). Continuous variables are presented as the means  $\pm$  standard deviations if they followed a normal distribution, and differences between groups were assessed via t tests. Alternatively, continuous variables that did not follow a normal distribution are presented as medians (interquartile ranges), and group comparisons were performed using the Wilcoxon test. Categorical variables are reported as frequencies (percentages), and group differences were evaluated using either the chi-square test or Fisher's exact probability method. Statistical significance was considered when  $P < 0.05$ .

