### ***Physical Fitness***

The assessment of physical fitness parameters, including grip strength, walking speed, and balance, was conducted at two time points: upon admission and at the three-month follow-up. ① Grip strength was measured via an electronic grip device (manufacturer model: Guangdong Zhongshan Xiangshan Scale Instrument Co., Ltd. EH201R). During the measurement, a sitting position was maintained, the upper limbs naturally drooped at the side of the body, the palm faced the body, the grip metre handle faced outwards, the grip posture was adjusted according to palm size of the palm, and the grip metre was forced for measurement. A stable attitude was maintained during the measurement, and the grip metre was not swung back and forth. The grip strength of the dominant hand was measured 3 times, and the maximum value was taken as the final measurement result. ② Step speed: 4.6 m. The investigator used a stopwatch (model: new Dragon XL-011) to measure step speed in "s" (to 2 decimal places). ③ 30-s chair standing test: A straight back chair (sitting height of 43.2 cm) was used, and the patient was informed of the evaluation process and shown the movement before the test. The seat was placed against the wall, and the patient sat in a chair with their back straight, feet flat on the ground, and arms and

wrists crossed and held at the chest. When the test began, the patient completed 1-2 exercises, performed the preexperiment, and then started the timed test. The correct movement was as follows: completing the full standing position and then sitting down. If the patient's buttocks could touch the chair seat position, the above movements were repeated as much as possible within 30 s, and the effective number of movements was recorded. ④ BMI was calculated as follows:  $BMI = \text{body weight kg}/(\text{height m})^2$ ; and waist circumference per cm was measured.

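### Outcomes are compared by unadjusted t or Wilcoxon tests, although admission values are documented for several outcomes and no baseline outcome value is among the listed matching covariates

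*Combined protocol and SAP*

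**What the plan says.** The Statistical Method section is the whole comparison plan. For normally distributed continuous outcomes, "differences between groups were assessed via t tests"; for the others, "group comparisons were performed using the Wilcoxon test". Categorical variables go to a chi-square or Fisher test. No regression, analysis of covariance, mixed model or covariate is named.

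Allocation was not random. Study Design forms the groups by admission date, and the Randomization section relies on 1:1 propensity score matching: "The matching process involved considering covariates such as age, sex, education level, marital status, exercise habits, monthly salary, current address, living arrangement", continuing with "history of CHD, history of PCI, length of hospitalization, medical insurance status and polypharmacy data obtained from presurveys". That makes thirteen named items, introduced as examples. None is an admission value of 6MWT, SF-12, frailty, gait speed, grip strength, chair stand, waist circumference, BMI or a lipid. The Results section supports balance after matching only by P ≥ 0.05 and gives no standardised differences.

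On baseline data, Physical Fitness says that the assessment "was conducted at two time points: upon admission and at the three-month follow-up". Blood lipid indices places weight, height and lipids at admission and follow-up. The sections on 6MWT, frailty and SF-12 give no admission time point. A baseline for these is implied by the aim of assessing improvement (Study Purpose) and, for quality of life, by the time effects reported in the Discussion.

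**The concern.** When groups are formed by calendar date, nothing in the design guarantees similar function, quality of life or lipids at the start. The baseline value of an outcome is usually among its best predictors. If it enters neither the matching nor the outcome comparison, any starting difference passes in part into the 3-month contrast, and variance that could have been explained stays in the error term. The Discussion then attributes better functional status and lipids to the intervention. At stake are the precision of every continuous outcome and how far those contrasts can be read as effects of the programme.

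**Working it through.** The documents contain no sample-size calculation, power, effect size or SD, so there is no design figure to reproduce. The counts agree: 89 + 75 = 164 before matching and 68 + 68 = 136 after.

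**Inputs**
- n = 68 per arm (Randomization: "with 68 patients in the multidimensional digital cardiac rehabilitation group and 68 patients in the usual care group").
- Significance level 0.05 (Statistical Method). Sidedness is not stated; two-sided is assumed.
- Balance criterion P ≥ 0.05 (Results).
- Correlation r between admission and 3-month values: not given, assumed 0.3, 0.5 and 0.7.
- Effects are in SD units, with equal SD at both times and groups treated as independent (assumed).

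**Step 1. Standard error of a difference.** √(2/68) = 0.1715 SD.

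**Step 2. Largest baseline gap that still gives P ≥ 0.05.** t(0.975; 134) × SE = 1.978 × 0.1715 = 0.339 SD.

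**Step 3. Precision.** Relative to a 3-month-only test, the variance factor is 1 − r² with baseline adjustment and 2(1 − r) for a change score. The unadjusted test detects (1.960 + 0.842) × 0.1715 = 0.480 SD at 80% power (a reference value). Adjustment multiplies this by √(1 − r²).

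**Step 4. Carry-over of a baseline gap D.** It is r × D for a 3-month-only test and (r − 1) × D for a change-score test.

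| r | 1 − r² (cut) | 2(1 − r) | Unadjusted n per arm for equal precision, 68/(1 − r²) | Detectable difference with adjustment | r × 0.339 | (r − 1) × 0.339 |
|---|---|---|---|---|---|---|
| 0.3 | 0.91 (9%) | 1.40 | 75 | 0.458 SD | 0.10 SD | −0.24 SD |
| 0.5 | 0.75 (25%) | 1.00 | 91 | 0.416 SD | 0.17 SD | −0.17 SD |
| 0.7 | 0.51 (49%) | 0.60 | 133 | 0.343 SD | 0.24 SD | −0.10 SD |

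**Step 5. Effect on false positives for a 3-month-only test.** Given an observed baseline gap D and no true effect, the 3-month difference has mean r × D and variance (1 − r²) × SE², while the test rejects beyond 1.96 × SE. For r = 0.3, 0.5 and 0.7:
- D = 0.339 SD: 8%, 13% and 21%.
- D = 0.2 SD: 5.3%, 5.8% and 5.5%.
- D = 0.1 SD: 4.3%, 3.2% and 1.5%.

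The error rate is clearly raised only near the limit. At D = 0.1 SD the carry-over is just 0.03, 0.05 and 0.07 SD.

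**The case against.** The case on the other side is substantial, and most of it limits the point without removing it.

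- A reader might infer that admission 6MWT, SF-12 and frailty data are already held. The documents do not establish this. Study Outcome places all outcome measurements at three months. The in-hospital walk test in section 1.1 sets exercise intensity within the intervention package, and the Control group section says that controls had no specific individual exercise instruction. The explicit admission data are mostly for secondary outcomes, although gait speed and grip strength also feed the frailty score.
- A reader might infer that baseline values were certainly used nowhere. The covariate list is given as examples and may be incomplete. The Discussion's time effects also suggest some repeated-measures or within-group analysis. None of the tests in Statistical Method is described as producing a time effect, so the two sections do not match.
- The t test may be on change scores: Study Purpose speaks of improvement, and Study Outcome of changes in lipids. That reverses the sign of the carry-over. It is still not adjustment, and its variance exceeds that of the adjusted analysis at every correlation in the table.
- The 0.339 SD gap is a limit, not an observation, and it is not stated that the P ≥ 0.05 check covered the outcome measures. The groups come from adjacent months. If imbalance were chance alone, a gap that large would arise about 5% of the time and would already be inside the test's type I error. Systematic imbalance through consent or the restriction to complete data is possible but not shown.
- The Wilcoxon test is valid for a short ordinal frailty count. Proportional-odds regression and dropping the normality check are preferences.

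**Conclusion.** The point holds as an omission in the analysis plan that can be repaired at little cost. On the stated methods, the group comparisons are unadjusted and no baseline outcome value is a listed matching covariate, in a non-randomised study that documents several such values at admission. The gain from adjustment is a 9% to 49% cut in variance, and the worst-case carry-over is that in Step 4. Both rest on the assumed correlations, and the carry-over also on a gap at the limit of the balance check.

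It would be too strong to conclude that the reported effects are biased, or that the most important confounder has been shown to be uncontrolled. Neither the baseline differences nor the correlations are given. Nor would baseline adjustment make the comparison equivalent to a randomised one: calendar-period and unmeasured confounding would remain.

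**What to change.** - For each continuous outcome with an admission value in both groups, regress the 3-month value on group and its own baseline value, with standard errors that allow for the matched pairs. Because results are already reported, label this as a post hoc re-analysis.
- Report standardised baseline differences for the outcome measures after matching, and give the full list of matching covariates.
- State whether 6MWT, SF-12 and frailty were measured at admission in both groups. Where they were not, say that improvement in that outcome cannot be baseline-adjusted.
- Reconcile Statistical Method with the time effects in the Discussion: either describe the model that produced them or remove the statement. Say whether the group tests are on 3-month values or on changes.
- Do not add length of hospitalization to the outcome regression. The intervention starts in hospital, so length of stay may follow it.

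Proportional-odds regression for frailty and dropping the normality-driven choice of test are optional. So is adding baseline outcomes to the propensity model. With 75 controls before matching and thirteen covariates already named, that could cost overlap and matched pairs.

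The cost is analysis-plan wording and a re-analysis. No new data are needed where baselines exist in both groups; elsewhere the cost is a stated limitation.
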